**Fig 1 pone.0280163.g001:**
[figure not shown]
Schedule of enrolment, interventions, and assessments. The figure shows Standard Protocol Items: Recommendations for Interventional Trials (SPIRIT) schedule of enrolment, interventions and assessments information. **Post-allocation time points occur at 6 months intervals, starting when the first subject undergoes partial heart transplantation and continuing until one year after all subjects have been enrolled.

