### Study population

Five patients in need of a heart valve replacement will be included in the study. A study investigator who normally participates in our biweekly pediatric heart center case conference meeting and has access to patient records and surgical referrals for valve replacement will identify potential candidates for the trial. Study investigators will obtain permission from the primary cardiologist or cardiac surgeon prior to approaching parents or legal guardians to discuss participation in the trial. Telemedicine may be utilized to initially discuss the risks and benefits associated with the study with parents or legal guardians of potential subjects who are outpatients, but an in-person meeting will be required for a formal consent discussion. Expectant mothers who are carrying fetuses that are expected to require heart surgery requiring a valve replacement within the first two years of life may be approached for enrollment in the study as well.

The interventional portion of the study will take place in the cardiac operating rooms and in the Pediatric Cardiac Intensive Care Unit at Shawn Jenkins Children’s Hospital at MUSC. Additional observational data will be collected pre- and intraoperatively, and postoperatively on the Cardiac Stepdown Unit and in the outpatient cardiology clinics at MUSC’s Summey Medical Pavilion.

To be eligible to participate in this study, the patients can be either male or female and must meet the following inclusion and exclusion criteria:

Inclusion Criteria

Children less than 2 years of age who are referred for a cardiac operation that involves a primary semilunar valve replacement, or children less than 2 years of age who are referred for a cardiac operation involves an initial replacement of a previously placed prior homograft, bioprosthetic, or mechanical valve in the aortic or pulmonary positionDeemed acceptable for partial heart transplantation based on the standard evaluation process used for conventional orthotopic heart transplantation at our center (see S1 Appendix)Have insurance approvalProvide written informed consent of both parents or legal guardians; if there is only one parent or legal guardian, consent from that individual will be adequate.

Exclusion Criteria

Absolute contraindications for conventional orthotopic heart transplantation:

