#### Preoperative procedures

Written informed consent for partial heart transplantation will be obtained from the parents or legal guardians of each subject. Potential subjects and their parents or legal guardians will undergo a full evaluation for candidacy for partial heart transplant using well-established criteria and workflows for infants and young children who are being assessed for conventional heart transplantation. These patients will be listed for partial heart transplant using pre-established mechanisms similar to conventional heart transplantation via the regional South Carolina organ procurement network, We Are Sharing Hope.

For a subject to be enrolled in the trial, a time window will be established by an attending pediatric cardiologist as to how long the subject can be listed for partial heart transplantation before a conventional valve replacement option is scheduled. This time window will be determined based on the subject’s clinical status and severity of valve dysfunction and may be revised over time based on evolving clinical status.

As is the case for patients undergoing conventional heart transplantation, donor hearts will be selected based on the recipient’s ABO blood group, PRA, weight, CMV status, and EBV status. Parents or legal guardians of enrolled subjects will be required to carry a transplant pager, consistent with established practice for patients who are listed for conventional heart transplantation.

When a donor heart becomes available, a focused echocardiogram will be performed on the donor heart to specifically assess the semilunar valve annulus size and function before the heart is accepted. The donor heart will be procured and transported to MUSC by our cardiac surgeons using practices consistent with those utilized for conventional heart transplantation. The donor semilunar valve will be excised from the donor heart by a pediatric cardiac surgeon. The heart valve will be accepted after it is visually inspected by the procurement team at the donor hospital.

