#### Late postoperative procedures

Patients who reside outside of the greater Charleston area will be required to stay locally for six weeks at the Ronald McDonald House or elsewhere following hospital discharge, consistent with practice for patients recovering from conventional heart transplantation. Patients will receive follow-up care in our outpatient pediatric heart transplant clinic at intervals consistent with those used for infants and young children recovering from conventional heart transplantation.

Once deemed appropriate by the pediatric heart transplant attending, patients who reside outside of the greater Charleston area may have some of their outpatient cardiology clinic visits conducted by a local cardiologist. In such cases, communication between the pediatric heart transplant attending of the local cardiologist will occur consistent with established practices for children who have undergone conventional heart transplantation. Immunosuppression will be maintained at standard levels given in conventional heart transplantation for at least the first year following valve transplant.

Once patients have grown and further valve growth is no longer required, consideration may be given to weaning or discontinuing immunosuppression. Once immunosuppression is stopped the heart valve transplant will turn into a homograft and stop growing. We anticipate that once the homograft deteriorates, it may be replaced with a prosthetic valve. Follow-up by the research team will occur biannually in conjunction with clinically indicated visits until one year after the transplanted valve has been replaced.

If a patient dies, parents or legal guardians will be offered an autopsy. The aim of the autopsy should be not only to establish the cause of death as accurately as possible, but also to evaluate the effects of partial heart transplantation and to detect and delineate any intercurrent processes, both known and unsuspected.

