### Data management methods

Data will be collected at intervals as described above. Descriptions of confidentiality provisions and data safety monitoring boards (DSMB) are provided in a later section. In order to preserve the confidentiality of the participants, the following interventions will be undertaken:

A. Case report forms (CRFs) will be developed prior to the onset of the trial and completed by a study investigator for each patient.
a. An enrollment form will be completed once written informed consent is provided by the parents or legal guardians.b. Adverse event forms will be completed as needed throughout the operative hospitalization.B. A dedicated Excel database will be developed for the trial.
a. All data from the CRFs will be entered into a dedicated Excel database by a study team member.C. In the case of a subject withdrawing from the trial, the data will be potentially included in the final analysis depending on the time enrolled in the trial.

Missing data will be addressed by omission or analysis as appropriate. Sensitivity analysis will be planned to avoid misleading inference when complete-case analysis is performed.

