### Assessment of results

The primary outcomes will be the feasibility and safety of partial heart transplantation. The feasibility will be determined by the ability to perform the new operation in at least one patient per year for three years after enrollment opens. The safety of the procedure will be indicated by survival and re-interventions that are the same or are better than those reported in the literature for patients of similar age undergoing conventional valve replacement. Safety will primarily be defined as patient survival or re-operation or transcatheter reintervention on the transplanted valve at six-month intervals, starting six months after the first subject undergoes a valve transplant, and continuing until one year after all five subjects have been enrolled. Safety will also be assessed by tracking rates of immunosuppression side effects, including development of insulin-dependent diabetes, chronic renal insufficiency, and significant infections.

The secondary outcomes will be valve annulus growth over time, stenosis and regurgitation. The valve annulus diameter will be measured using echocardiography in two planes at baseline and every six months following the operation. The valve annulus Z-score should remain relatively unchanged over time, indicating an increase in valve annulus growth corresponding with an increase in body surface area. This change should correspond to the growth of conventional heart transplants and Ross pulmonary autografts [18–20]. Valve stenosis and regurgitation will be assessed via transthoracic echocardiogram with pulse Doppler and with color Doppler, respectively, every six months following the operation.

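### The primary safety window closes one year after the last enrolment, not the last transplant, so the last subject has at most 12 months of post-transplant time in it and no guaranteed minimum

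*Protocol article*

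**What the plan says.** Protocol article, Assessment of results, defines the primary safety outcome: "Safety will primarily be defined as patient survival or re-operation or transcatheter reintervention on the transplanted valve at six-month intervals". The readings run "starting six months after the first subject undergoes a valve transplant, and continuing until one year after all five subjects have been enrolled". The legend to Fig 1 uses the same two anchors for the schedule of assessments: "starting when the first subject undergoes partial heart transplantation and continuing until one year after all subjects have been enrolled".

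The same Assessment of results section times the secondary outcomes (annulus growth, stenosis, regurgitation) differently, at six-month steps from each subject's own operation.

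Two sections place enrolment before the transplant. Data management methods says "An enrollment form will be completed once written informed consent is provided by the parents or legal guardians". Preoperative procedures says "Parents or legal guardians of enrolled subjects will be required to carry a transplant pager", so an enrolled child is still waiting for a donor. That section also has a cardiologist set, for each subject, how long the child can stay listed before a conventional valve is scheduled. This limit "may be revised over time based on evolving clinical status".

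Late postoperative procedures describes a longer follow-up: "Follow-up by the research team will occur biannually in conjunction with clinically indicated visits until one year after the transplanted valve has been replaced". The article does not say how this relates to the primary safety outcome.

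**The concern.** Safety is to be judged by whether survival and re-intervention are at least as good as published results for conventional valve replacement at a similar age. Re-intervention accumulates with time since surgery. The Introduction says that valve implants fail over time, and the homovital valve series it cites is reported at 5 and 10 years. A fair reading of five children against such results needs to know how long each child was observed after the operation.

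The stated window does not secure this. Its start depends on the first subject's surgery and its end on the last subject's consent. How much post-transplant time the last child contributes depends on how long a donor takes to appear, and no minimum is set. With five subjects, one child is 1/5 = 20% of the sample.

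**Working it through.** The article derives no figure on this point, so there is none to reproduce. The check is timing arithmetic on the stated rule.

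**Inputs from the article**
- Closure of the primary window: 12 months after the fifth enrolment (Assessment of results; Fig 1 legend).
- Reading interval: 6 months, counted from the first transplant (same places).
- Enrolment precedes transplant (Data management methods; Preoperative procedures).
- Sample size: 5 (Study population).

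**Input assumed**
- w, the months from enrolment to transplant for the last subject. The article gives no value, so a range is shown.

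**Step 1. Post-transplant time of the last subject inside the window.** Time = max(0, 12 - w). The number of complete six-month intervals on the subject's own clock is the whole part of that time divided by 6. The number of calendar readings that fall after the subject's transplant depends on where the transplant lies on the six-month grid, so a range is given.

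| w (months, assumed) | Post-transplant time in window (months) | Complete six-month intervals, own clock | Calendar readings after transplant |
|---|---|---|---|
| 0 | 12 - 0 = 12 | 2 | 2 |
| 3 | 12 - 3 = 9 | 1 | 1 to 2 |
| 6 | 12 - 6 = 6 | 1 | 1 |
| 9 | 12 - 9 = 3 | 0 | 0 to 1 |

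Twelve months is therefore a ceiling, reached only with no wait. Once w exceeds 6, the last subject has no complete six-month interval in the window. Arithmetically the time reaches zero at w = 12.

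**Step 2. Time since surgery at the first reading.** A subject transplanted t months after the first subject meets the next calendar reading 6 - (t mod 6) months after surgery. For t = 1 this is 5 months, for t = 5 it is 1 month, and for t = 6 it is 6 months. One calendar reading therefore tabulates children at different times since surgery.

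**Step 3. Spread across subjects.** Suppose one enrolment a year, an assumption borrowed from the minimum operating rate in the feasibility criterion, and no wait for the first subject. The fifth enrolment then falls 4 x 12 = 48 months after the first. At closure the first subject has 48 + 12 = 60 months and the last has 12 - w, for example 9 at w = 3.

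**Step 4. Effect on a simple proportion.** If the last subject has a re-intervention after closure, a crude count within the primary window shows E/5 where the longer follow-up shows (E + 1)/5, a difference of 20 percentage points. A time-to-event summary would treat that subject as censored at 12 - w months and would not count the child as event-free beyond that point.

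**The case against.** Several stronger readings are tempting, and the document does not support them.

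- **That the clocks contradict each other.** A primary window can sit inside a longer follow-up. What is missing is a sentence relating the two.
- **That re-interventions are hidden.** Research follow-up continues twice a year until well past the window, so later events would still be recorded. They would only fall outside the primary outcome.
- **That the wait is open-ended.** The listing time is set for each subject, although it can be revised and no length is stated.
- **That the last subject may have no follow-up at all, through prenatal enrolment.** Study population allows an approach to "Expectant mothers who are carrying fetuses that are expected to require heart surgery requiring a valve replacement within the first two years of life". But the inclusion criteria require a child under two who has been referred for a valve operation and accepted after transplant evaluation, so a prenatal approach need not start the enrolment clock. A wait of 12 months or more is not excluded, but nothing shows it to be likely.
- **That the comparison with the literature is biased.** The comparator rates are not given, so it cannot be said that they refer to a fixed time after surgery. The one durability series described gives actuarial rates, which allow for unequal follow-up. Staggered entry with a common closing date is ordinary administrative censoring. It misleads only if crude proportions are used, and the article names no summary beyond descriptive statistics.

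Two further points carry weight. Deaths and re-operations are dated events, so the calendar grid does not change whether or when they happened, only how they are tabulated. And the term for enrolment may be used loosely: the data safety monitoring board reviews data one month after each of the first three enrolments, which fits best if enrolment is close to transplant. On that reading the last subject would have about 12 months. The enrolment form and the transplant pager point the other way.

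These objections limit the size of the problem. They do not supply a minimum post-transplant time, and they do not explain why the primary outcome uses a clock that the secondary outcomes avoid.

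**Conclusion.** The point holds in a limited form. As written, the last subject contributes at most 12 months after transplant to the primary safety outcome, and 12 - w months after a wait of w: 9 at w = 3, 6 at w = 6. Subjects are also read at unequal times since surgery. This rests on taking enrolment as consent and listing, which the enrolment form and pager wording support. How often a short follow-up would occur cannot be computed, because no waiting time is given. Re-intervention would be understated against the literature only if the results are reported as simple proportions.

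This is a rule the article states, not a detail left to an analysis plan. It should be fixed. It is not critical: this is a five-subject descriptive pilot with an independent monitoring board, and data collection runs beyond the window.

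**What to change.** 1. In Assessment of results, time the primary safety readings from each subject's own transplant (6 months, 12 months and so on), as is already done for the secondary outcomes.
2. Close the primary safety outcome when the last transplanted subject reaches 12 months after transplant. Every transplanted subject then has at least 12 months and two readings, or an earlier event or withdrawal, whatever the wait.
3. State that the follow-up in Late postoperative procedures is the longer-term extension of the primary window.
4. Align the Fig 1 legend with Assessment of results. The legend starts at the first transplant and the text six months later; both should use the per-subject clock.

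The cost is protocol wording and a later closing date. Closure moves by the last subject's wait, for example 3 months if w = 3. No visits are added, because the existing follow-up already runs longer. The 12-month minimum keeps the one-year figure the article already uses and only moves its anchor from enrolment to transplant.

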## Introduction

Congenital heart defects are the most common type of birth defects in humans. In North America, 7 in 1000 live born children are affected [1]. Worldwide, this causes over 180,000 infant deaths per year [2]. Treatment of congenital heart defects frequently involves heart valve replacement. However, infants and young children who undergo valve replacements uniformly outgrow their valve implants, which always become dysfunctional over time due to the development of stenosis, regurgitation, or a combination of the two. As a result, serial cardiac reoperations to exchange the valve implants for successively larger versions are necessary as infants and children grow [3]. Additionally, current procedures in infants and neonates, such as the Ross procedure, have been known to cause substantial adverse effects. The Ross procedure has particularly high mortality in neonates [4, 5]. Children aged under one year who had undergone the Ross procedure also had a higher frequency of re-intervention postoperatively [4].

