
Partial heart transplantation contributes a new approach to solve the problems with the current management for valve dysfunction in neonates, infants and young children [13]. Partial heart transplantation uses living homografts. Living homografts differ from conventional homografts in three important aspects: (1) The valves utilized in partial heart transplants will be procured to minimize the ischemic time just like conventional heart transplants, whereas homovital homografts are procured from donors at autopsy after a long period of ischemic time.

(2) Partial heart transplants will be implanted within six hours (similar to conventional orthotopic heart transplants), whereas the ischemia time for homografts is typically much longer.

(3) Recipients of a partial heart transplant will be immunosuppressed in the same way as conventional orthotopic heart transplant recipients, whereas recipients of a homograft are not typically immunosuppressed.

These differences should preserve viability of the partial heart transplant and allow it to grow, similar to the growth of a conventional orthotopic heart transplant.

Our central hypothesis for this trial is that transplantation of a living homograft (“partial heart transplantation”) will be associated with superior outcomes compared to currently available implants (homografts, bioprostheses, mechanical valves, non-valved conduits) in infants and young children. Partial heart transplants may replace either a single semilunar valve or both semilunar valves depending upon the patient’s needs. We will test our central hypothesis, and thereby achieve the objective of this trial by studying the following specific aims.

The primary aim is the feasibility and the safety of partial heart transplantation. Complication rates are expected to be similar or better to those of young children who have undergone orthotopic heart transplantation [14]. Secondary aims to be studied are valve annulus growth, stenosis, and regurgitation. We anticipate that stenosis and regurgitation will be minimal, and transplanted valve function will be similar to semilunar valve function observed in conventional heart transplants [15].

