### Treatment

The evaluations, tests, and procedures below are typically performed as standard clinical care for recipients of a conventional heart transplant or heart valve replacement. No additional study-specific tests or procedures are planned as part of this trial. We will obtain all the information necessary for the research from the electronic medical record as would be consistent with standard practice for a conventional heart transplant or heart valve replacement.

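### Pulsed Doppler is the only mode named for stenosis, a secondary outcome, and its velocity limit leaves fast jets unreliably quantified at many plausible settings

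*Protocol article*

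**What the plan says.** Under Assessment of results, the protocol article lists the secondary outcomes: "The secondary outcomes will be valve annulus growth over time, stenosis and regurgitation". It then names the instruments, on a six-monthly schedule after surgery: "Valve stenosis and regurgitation will be assessed via transthoracic echocardiogram with pulse Doppler and with color Doppler, respectively". The word *respectively* pairs stenosis with pulsed Doppler and regurgitation with color Doppler. The article gives no other Doppler mode, velocity, gradient or grading scale for stenosis.

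Two other places bear on the point. The Introduction describes existing valve implants as ones "which always become dysfunctional over time due to the development of stenosis, regurgitation, or a combination of the two", and states the expectation for the transplanted valve: "We anticipate that stenosis and regurgitation will be minimal". The Treatment section says where the measurements come from: "No additional study-specific tests or procedures are planned as part of this trial", and "We will obtain all the information necessary for the research from the electronic medical record". The Data analysis section plans descriptive statistics only, for five participants without a control group.

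**The concern.** Pulsed Doppler samples at one chosen depth and must wait for each echo before sending the next pulse. This sets a maximum velocity that it can read unambiguously. Above that limit the signal aliases, and the peak velocity, and so the gradient derived from it, can no longer be read directly. A narrowed semilunar valve produces a fast jet, so the named mode suits a valve with little or no stenosis and becomes less informative as stenosis worsens. Continuous-wave Doppler does not have this limit.

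The Introduction names stenosis as one way in which current implants fail and expects little of it here. A method that loses precision at the upper end of the scale is a poor choice for checking that expectation. With five patients, each valve is 1/5 = 20% of the data, so even one valve recorded only as above the limit would matter to a descriptive summary.

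**Working it through.** The article states no velocity, gradient or threshold for stenosis, so there is no figure of its own to reproduce. The check is whether the named mode can read the velocities of a stenotic valve.

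**Inputs**
- From the article: pulsed Doppler is the mode for stenosis (Assessment of results); children are under 2 years at entry (Study population).
- Assumed, because the article gives none: speed of sound c = 1540 m/s; transducer frequency f of 3, 5 or 8 MHz; sample depth d of 3, 5 or 7 cm; beam parallel to flow.

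**Formulas**
- Velocity limit: v = c²/(8·f·d), with f in Hz and d in metres.
- With full baseline shift: 2v.
- Gradient in mmHg from a velocity in m/s: 4 × velocity².

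**One setting in full: 5 MHz, 5 cm**
- c² = 1540² = 2,371,600.
- 8·f·d = 8 × 5,000,000 × 0.05 = 2,000,000.
- v = 2,371,600 / 2,000,000 = 1.19 m/s; gradient 4 × 1.186² = 5.6 mmHg.
- Shifted: 2.37 m/s; gradient 4 × 2.372² = 22.5 mmHg.

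**Ceiling with full baseline shift, over the assumed range**

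| | 3 cm | 5 cm | 7 cm |
|---|---|---|---|
| 3 MHz | 6.59 m/s (174 mmHg) | 3.95 m/s (62 mmHg) | 2.82 m/s (32 mmHg) |
| 5 MHz | 3.95 m/s (62 mmHg) | 2.37 m/s (22 mmHg) | 1.69 m/s (11 mmHg) |
| 8 MHz | 2.47 m/s (24 mmHg) | 1.48 m/s (9 mmHg) | 1.06 m/s (4 mmHg) |

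Without baseline shift each velocity is halved and each gradient is divided by four.

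**Comparison with jets of interest**
- A gradient of 36 mmHg corresponds to √(36/4) = 3.0 m/s, and 64 mmHg to √(64/4) = 4.0 m/s. These are reference points for the arithmetic, not thresholds from the article.
- With full baseline shift, six of the nine settings have a ceiling below 3.0 m/s. Eight of nine are below 4.0 m/s, two of them only just (3.95 m/s).
- Without baseline shift, only 3 MHz at 3 cm (3.29 m/s) reaches 3.0 m/s, and no setting reaches 4.0 m/s.

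The nine settings are a grid and not a sample of actual practice, so these counts show sensitivity to the settings, not a frequency.

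**The case against.** **Stenosis could still be graded.** A reader might infer that significant stenosis cannot be graded at all under this plan. The documents do not support that. Shallow or low-frequency settings with baseline shift resolve jets of 3 m/s and, at 3 MHz and 3 cm, well beyond 4 m/s; shallow depths are plausible in children this young. Aliasing is visible on the trace and itself shows that the velocity exceeds the limit. The Treatment section also takes the data from standard clinical echocardiograms in the medical record, and nothing in the article excludes other modes, so continuous-wave readings may already be there. All of this stands. What it leaves untouched is that the outcome definition tells whoever completes the case report form which reading to take, and it names the pulsed one. Some follow-up may also take place with local cardiologists (Late postoperative procedures), which makes an explicit definition more useful.

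**The detail belongs in the full protocol.** Echo acquisition settings are commonly left out of an article. That would answer a silence, but here the article names a mode.

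**The error favours the hypothesis.** A reader might infer that stenosis would be recorded as falsely low. That does not follow, because an aliased trace need not be entered as a low value. Nor is stenosis the main check on growth: Assessment of results measures annulus diameter and its Z-score directly, and counts reintervention on the valve under safety.

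**No baseline.** The annulus has a stated baseline reading and stenosis and regurgitation do not, so a reader might infer that an early gradient or leak would be mistaken for a later one. The article answers this. Operative procedures collects the size and function of the implanted valve from the intraoperative echocardiogram as research data, and Early postoperative procedures provides for transthoracic echocardiograms after surgery. This is not part of the point.

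**Conclusion.** The point holds as a minor measurement correction. The article assigns stenosis to pulsed Doppler alone, and under assumed settings of 3 to 8 MHz and 3 to 7 cm the baseline-shifted ceiling lies anywhere from about 1.1 to 6.6 m/s. Followed literally, the sentence would leave jets of 3 to 4 m/s ambiguous or known only to exceed a limit at many of those settings.

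The limit itself is physics. Its size in this trial depends on frequency, depth and baseline setting, none of which the article gives, and the practical loss would be small if continuous-wave readings are already in the clinical record. Only a descriptive secondary outcome in five patients is affected; no sample size, primary outcome or decision rule depends on it.

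**What to change.** Replace the sentence on stenosis and regurgitation in Assessment of results with wording to this effect: stenosis will be assessed by peak velocity and by peak and mean gradient on continuous-wave Doppler across the transplanted valve; pulsed Doppler will be used for the velocity proximal to the valve; regurgitation will be assessed by color Doppler; all readings will be taken from the same standard-care transthoracic echocardiogram, on the six-monthly schedule already stated.

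Add a field to the echo case report form for the continuous-wave readings.

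The cost is one sentence and one form field. Because the readings come from the same standard-care echocardiogram, no study-specific test or visit is added, so the commitment in the Treatment section is kept.
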